### Statistical methods

Demographics will be presented and values of IS and MVO will be summarised, both overall and by treatment group. The distribution of IS will be investigated and the data will be transformed if found to be non-normally distributed. Primary analysis will be by intention to treat with a secondary analysis by treatment received. Patients entering into the study but not completing the CMRI will continue to be followed-up for MACE on an intention-to-treat basis. Analysis of Variance (ANOVA) will compare mean IS between groups. Each drug will be compared to the control (that is, Adenosine *vs.* Control and SNP *vs.* Control). Multivariable analysis using linear regression will take into consideration possible confounders such as sex, age and other co-morbidities. The major confounders of location of infarct (anterior/non-anterior) and time from symptom onset to reperfusion will be addressed by the stratified randomisation process. Other important confounders, such as collateral blood flow to the infarct territory determined by the Rentrop score [98], will be controlled for in the statistical analysis. Secondary endpoint analysis will employ time-to-event regression methods to investigate potentially important predictors of MACE.

### Sample size

Sample size has been based on previous observations of significant correlation between the extent of CMR measured MVO and IS (which on average is 20% of LV mass as detected by CMR after P-PCI) [16]. Since there are no available data regarding the incidence of MVO with the study drugs assessed by CMR, and the wealth of published data on IS following P-PCI, we have chosen IS as the primary endpoint of the trial. IS is a powerful predictor of ventricular function, adverse LV remodeling and short-medium term clinical outcome [13, 15, 16, 99–111]. Furthermore, new infarct size of 4% of LV mass has been shown to be associated with adverse prognosis in patients with coronary artery disease undergoing revascularisation-related injury [112]. To detect a reduction in IS from 20% to 15% of LV mass, assuming a standard deviation of 10% [18, 102, 108, 109, 113–117], α of 0.05, two-tailed, 80% power and a drop-out rate of 20% between P-PCI and CMR, 80 subjects per group (240 in total) will be required.

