**Methods:**

The REperfusion Facilitated by LOcal adjunctive therapy in STEMI (REFLO-STEMI) trial is a multicentre, prospective, randomised, controlled, open label, study with blinded endpoint analysis: Patients presenting within 6 h of onset of STEMI and undergoing planned primary PCI (P-PCI) with TIMI 0/1 flow in the infarct-related artery (IRA) and no significant bystander coronary artery disease on angiography, are randomised into one of three groups: PCI with adjunctive pharmacotherapy (intracoronary adenosine or SNP) or control (standard PCI). All receive Bivalirudin anticoagulation and thrombus aspiration. The primary outcome is infarct size (IS) (determined as a percentage of total left ventricular mass) measured by cardiac magnetic resonance imaging (CMRI) undertaken at 48 to 72 h post P-PCI. Secondary outcome measures include MVO (hypoenhancement within infarct core) on CMRI, angiographic markers of microvascular perfusion and MACE during 1-month follow-up. The study aims to recruit 240 patients (powered at 80% to detect a 5% absolute reduction in IS).

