## Discussion

The REFLO-STEMI study has been designed to address the weaknesses of previous trials, which have collectively failed to demonstrate whether adjunctive pharmacotherapy with adenosine and/or SNP can reduce measures of myocardial injury (infarct size and MVO) and improve clinical outcome, despite good basic evidence that they have the potential to attenuate this process. The REFLO-STEMI trial will be the first study to combine what are considered appropriate efficacious drug dosages, delivered optimally to the site of maximal benefit, with the use of CMR to robustly measure reperfusion success, in a group of patients treated with a contemporary reperfusion strategy. The study will be powered accordingly to deliver a definitive answer as to whether these agents can reduce infarct size. Additional measures of myocardial perfusion (angiographic and electrocardiographic) and early clinical outcome data will provide further insight in to the potential role of prophylactic adjunctive pharmacotherapy, administered universally for STEMI patients or for those selected by retrospective analyses to most benefit, augmenting the benefits of timely-delivered P-PCI. As the largest and most scientifically robust trial to date, the REFLO-STEMI study, alongside the existing combination of studies, will inform future STEMI Guideline committees.

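### The 80 per group is sized for one two-group comparison, while the plan makes two against a shared control and does not say whether the 0.05 and the 80% are per comparison or for the trial

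*Protocol article*

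**What the plan says.** All references are to the protocol article.

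- **Sample size** gives one calculation. The target is "To detect a reduction in IS from 20% to 15% of LV mass", "assuming a standard deviation of 10" percentage points, with "α of 0.05, two-tailed, 80% power and a drop-out rate of 20% between P-PCI and CMR, 80 subjects per group (240 in total".
- **Statistical methods** compares mean infarct size between the three groups by ANOVA and adds: "Each drug will be compared to the control". The two contrasts are adenosine against control and SNP against control. The section does not say whether the ANOVA must be significant first. It leaves infarct location and time to reperfusion to the stratified randomisation and does not name them as terms in the primary model.
- **Abstract, Methods** describes the trial as "powered at 80% to detect a 5% absolute reduction in IS", without saying for which comparison or claim.
- **Discussion** goes further: "The study will be powered accordingly to deliver a definitive answer as to whether these agents can reduce infarct size".
- **Methods** fixes 1:1:1 allocation, stratified by symptom-to-balloon time, anterior infarction and centre.
- **Trial status** reports 247 recruited, with investigators still blinded to outcome data.

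**The concern.** A single alpha and a single power figure are quoted for a trial that has two chances of success on its primary outcome. Alpha 0.05 with 80% power describes one drug against control. It does not describe the trial as a whole, and the stated aims are partly about the trial as a whole: the Abstract's discussion, the end of the Background and the Discussion all ask whether adenosine or SNP reduces infarct size.

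Two misreadings are at stake. If each contrast is tested at 0.05, a conclusion that adjunctive drug therapy works, based on whichever drug succeeds, carries more than a 5% false-positive risk. If 0.05 is held for the trial, a null result for one drug would be taken as coming from an 80%-powered comparison when the power was lower. With recruitment closed, a later analysis plan can choose the multiplicity rule, but a rule alone cannot bring back 80% per drug.

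**Working it through.** **Inputs.** From Sample size: difference δ = 5 points, SD σ = 10, two-sided α = 0.05, power 80%, loss 20%. From Methods: equal allocation. From Statistical methods: two contrasts with one control, so the two test statistics have correlation ρ = 0.5.

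**1. The plan's own figure.** Normal approximation: n = 2σ²(z₀.₉₇₅ + z₀.₈₀)²/δ² = 2 × 100 × (1.960 + 0.842)²/25 = 62.8, so 63 per arm, and 63/0.8 = 78.75, so 79. The exact two-sample t-test needs 64 (power 0.801), and 64/0.8 = 80. The stated figure is reproduced exactly as one two-group comparison.

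**2. Reading A: 0.05 for each comparison.**
- Each drug: power 0.801.
- Both drugs inert: P(at least one significant) = 1 − P(|Z₁| < 1.96, |Z₂| < 1.96; ρ = 0.5) = 0.091.
- Both drugs give 5 points: each statistic has mean 5/(10√(2/64)) = 2.83. P(both significant) = 0.697 by bivariate normal, or 0.693 by simulation with estimated variance. P(at least one significant) is about 0.92.

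**3. Reading B: 0.05 for the trial, 64 evaluable per arm.**

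| Rule | Threshold | Power per drug | Evaluable (randomised) per arm for 80% |
|---|---|---|---|
| Bonferroni | α = 0.025 each | 0.712 (t), 0.721 (normal) | 77-78 (97-98) |
| Dunnett | 2.21 (normal), 2.23 (189 df) | 0.725 (t), 0.731 (normal) | about 75 (about 94) |

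The 247 recruited give 247/3 × 0.8 ≈ 66 evaluable per arm if arms are equal. Bonferroni power is then about 0.735, so the picture does not change.

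**4. The ANOVA.** As a test in its own right, the omnibus F has noncentrality λ = n Σ(μᵢ − μ̄)²/σ².
- Means (20, 15, 15) or (20, 15, 20): λ = 64 × 16.67/100 = 10.7, power 0.835.
- Means (20, 15, 17.5): λ = 64 × 12.5/100 = 8, power 0.710.

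If F were used as a gate before unadjusted contrasts (400,000 simulated trials), power for a drug with the full 5-point effect would be:
- 0.758 if the other drug is inert;
- 0.761 if the other drug also gives 5 points;
- 0.700 if the other drug gives 2.5 points.

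The chance of any false drug claim with both drugs inert would be 0.041.

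**5. Covariates in the primary model.** If the stratification factors explain a share R² of the variance, the residual SD is 10√(1 − R²). The document gives no R², so a range is shown (Dunnett, 189 df, 64 per arm):

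| R² (assumed) | Residual SD | Dunnett power per drug |
|---|---|---|
| 0 | 10.0 | 0.73 |
| 0.05 | 9.75 | 0.75 |
| 0.10 | 9.49 | 0.77 |
| 0.15 | 9.22 | 0.80 |
| 0.20 | 8.94 | 0.82 |

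**The case against.** The best reply is that nothing in Sample size labels 0.05 as a trial-level rate. Statistical methods poses two separate questions about two pharmacologically different drugs, and many statisticians would not adjust for that. Read this way, each drug has alpha 0.05 and 80% power, and the stated design is coherent. This stands. A reader might infer that the design cannot have both its stated alpha and its stated power. That conclusion needs the 0.05 to be family-wise, which the document never says.

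Two further replies also stand. First, a reader might infer that the three-group ANOVA contradicts the two-group sample size. But the text does not make it a gate. It may simply be the model that supplies the contrasts, and the omnibus F has 83.5% power when one drug has the full effect and the other has full or no effect. Second, the choice of multiplicity rule is ordinary analysis-plan content, and its absence from a condensed article is no fault.

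Two things survive. The article gives one unqualified power figure and attaches to it a definitive answer on both agents, in a trial whose aims are phrased as either-drug claims. And if 0.05 is meant for the trial, neither Dunnett nor Bonferroni, nor the ANOVA used as a gate, gives 80% per drug at this size without help from covariates. The 9% applies to the claim that at least one drug works, not to a claim about one named drug. The 69% for showing both drugs contradicts no promise in the text, but it does limit what a definitive answer on both can mean.

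**Conclusion.** The point holds as a qualification of the alpha and power claims. The calculation of 80 per group is correct for one drug against control. Applied per comparison, it gives about 80% power per drug, about 9% family-wise error, and about a 69% chance of showing both drugs when both work. Applied to the trial at 0.05, it gives about 73% per drug with Dunnett or 71-72% with Bonferroni, a loss of 7 to 9 points. Only if the ANOVA were made a gate would power per drug be 70-76%.

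These figures rest on the document's own δ, SD and loss rate, equal arms, 64 evaluable per arm and no covariate adjustment. The consequence is moderate: the trial is not undersized for the comparison it calculated, but the claim needs its scope stated before results are read.

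**What to change.** Before unblinding:

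1. Name the two drug-control contrasts as the primary tests, and state that the omnibus F is not a condition for them.
2. State whether alpha and power are per comparison or for the trial, and make the Abstract, Sample size and Discussion agree. Either wording is defensible: Dunnett-adjusted p-values with simultaneous intervals and about 73% power per drug before covariate adjustment; or unadjusted contrasts with 80% per comparison and the family-wise error of about 9% disclosed. The either-drug phrasing of the aims favours the first.
3. Put infarct location, time to reperfusion and centre in the primary model instead of relying on the stratified randomisation alone. Do not quote a power gain as fact: a return to about 80% under Dunnett needs an R² of about 0.15, which the document does not support with data.

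The cost is wording, one model specification and, on the first option, a less favourable stated power. No extra patients are needed.

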### Study organisation

The study is funded by the Medical Research Council (MRC) and managed by the National Institute for Health Research (NIHR) on behalf of the MRC-NIHR partnership. The trial sponsor is the University Hospitals of Leicester NHS Trust. Trial support will be provided by the Leicester Clinical Trials Unit (UK Clinical Research Collaboration (UKCRC) ID 43) who will be responsible for database provision, data management and statistical analysis. The study will be overseen by a Trial Steering Committee (TSC), with an independent chair and two additional independent members, which will have access to the database after study completion and data-lock. Efficacy and safety data (particularly unexpected adverse events) will be scrutinised by an Independent Data and Safety Monitoring Board (DSMB), which will report back to the TSC. Clinical trials number http://NCT01747174 Clinicaltrials.gov.

## Discussion

The REFLO-STEMI study has been designed to address the weaknesses of previous trials, which have collectively failed to demonstrate whether adjunctive pharmacotherapy with adenosine and/or SNP can reduce measures of myocardial injury (infarct size and MVO) and improve clinical outcome, despite good basic evidence that they have the potential to attenuate this process. The REFLO-STEMI trial will be the first study to combine what are considered appropriate efficacious drug dosages, delivered optimally to the site of maximal benefit, with the use of CMR to robustly measure reperfusion success, in a group of patients treated with a contemporary reperfusion strategy. The study will be powered accordingly to deliver a definitive answer as to whether these agents can reduce infarct size. Additional measures of myocardial perfusion (angiographic and electrocardiographic) and early clinical outcome data will provide further insight in to the potential role of prophylactic adjunctive pharmacotherapy, administered universally for STEMI patients or for those selected by retrospective analyses to most benefit, augmenting the benefits of timely-delivered P-PCI. As the largest and most scientifically robust trial to date, the REFLO-STEMI study, alongside the existing combination of studies, will inform future STEMI Guideline committees.

## Trial status

The REFLO-STEMI trial has successfully completed recruitment of 247 patients. Follow-up and data collection are in progress and all investigators remain blinded to outcome data.

## Abbreviations

AAR: Area at risk
ACC: American College of Cardiology
ACE: Angiotensin converting enzyme
ANOVA: Analysis of variance
CHF: Congestive heart failure
CK-MB: Creatine kinase MB isoenzyme
CMRI: Cardiac magnetic resonance imaging
CS: Cardiogenic shock
cTFC: Corrected TIMI frame count
CVD: Cardiovascular death
CVE: Cerebrovascular event
DSMB: Data and Safety Monitoring Board
ECG: Electrocardiogram
ESC: European Society of Cardiology
EGE: Early gadolinium enhancement
eGFR: Estimated glomerular filtration rate
FWHM: Full width half maximum
GPIIbIIIa: Glyocprotein IIbIIIa
Hs-CRP: High sensitivity C-reactive protein
IRA: Infarct-related artery
IC: Intra-coronary
IMH: Intra-myocardial haemorrhage
IS: Infarct size
LAX: Long axis
LBBB: Left bundle branch block
LCA: Left coronary artery
LGE: Late gadolinium enhancement
LV: Left ventricular
LVEDV: LV end-diastolic volume
LVEF: LV ejection fraction
LVM: LV end-diastolic mass
MACE: Major adverse cardiac events
MBG: Myocardial blush grade
MBV: Myocardial blood volume
MCE: Myocardial contrast echocardiography
MRC: Medical Research Council
MSI: Myocardial salvage index
MVD: Multi vessel disease
MVO: Microvascular obstruction
NIHR: National Institute for Health Research
N-IRA: Non-infarct related artery
NR: No-reflow
NT-proBNP: N-terminal pro-brain natriuretic peptide
NYHA: New York Heart Association
OS: Observational study
P-PCI: Primary percutaneous coronary intervention
RCA: Right coronary artery
ROI: Region of interest
SAX: Short axis
SBP: Systolic blood pressure
SD: Standard deviations
SNP: Sodium nitroprusside
SPAMM: Spatial modulation of magnetisation
SSFP: Steady state free precession
STEMI: ST-elevation myocardial infarction
STD: ST-segment deviation
STR: ST-segment resolution
SPECT: Sestamibi single-photon emission computed tomography
T2W: T2-weighted
T2w-STIR: T2W short tau inversion recovery
TA: Thrombus aspiration
TIA: Transient ischaemic attack
TIMI: Thrombolysis in Myocardial Infarction
TFG: TIMI flow grade
TLR: Target lesion revascularisation
TMPG: TIMI myocardial perfusion grade
TSC: Trial Steering Committee
TVR: Target vessel revascularisation
UKCRC: United Kingdom Clinical Research Collaboration.
